#### Follow-up with the SaNOK

Follow-up bereavement aftercare will be offered to SaNOK as part of the donation conversation process. An invitation to participate in the follow-up interview and the participant information sheet and consent form are posted to SaNOK who agreed to follow-up approximately two weeks before the 90-day post bereavement time point. Written or verbal consent are subsequently sought from the SaNOK for the follow-up interview and to audio-record it, although the interviewer will take notes rather than audio-recording if participants prefer. This contact procedure is similar to that used in previous research with families of potential organ donors [43]. Hence the three-stage process for consent to follow-up entails:Initial verbal consent to the offer of bereavement aftercare, followed byProvision of written information and written or verbal consent, andConfirmation of consent before conducting the interview, and for audio-recording.

The OTDS Family Support Coordinator conducts the telephone interviews with senior next of kin who agree to bereavement aftercare. Data sought include: demographic details; bereavement support received; information received regarding organ and tissue donation, and family members’ perception as to whether this was adequate for them to make a decision; previous discussions with their relative regarding organ and tissue donation; if they would now make the same donation decision, and their decision rationale.

#### Consent rates over time

To describe trends in family donation decisions over the same time period as the COMFORT study and identify any trends/changes over time notification data from all NSW hospitals ICUs and Emergency Departments are collected. Data variables collected have been listed at *Donation events*, above (with the addition of ethnicity, religion, ICU stay and retrieval data as appropriate).

### Statistical methods

The sample size calculation was performed using the Simon’s two-stage design [44]. 140 eligible next of kin families are required to be approached to provide consent for organ donation. This will yield 80% power with 95% confidence to exclude a consent rate of 29% in favour of a clinically worthwhile rate of 40% for the intervention. An eligible next of kin family are those of patients who had not registered their donation decision.

Additionally, in the first 46 eligible next of kin families who are approached, if less than 15 have consented to organ donation, consideration will be given to modifying the study.

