**Methods:**

This multicentre study is being performed in nine intensive care units with follow-up conducted by the Organ and Tissue Donation Service in New South Wales (NSW) Australia. The control condition is pre-intervention usual practice for at least six months before each site implements the intervention. The COMFORT intervention consists of six elements: family conversations regarding offers for organ donation to be led by a “designated requester”; family offers for donation are deferred to the designated requester; the offer of donation is separated from the end-of-life discussion that death is inevitable; it takes place within a structured family donation conversation using a “balanced” approach. Designated requesters may be intensivists, critical care nurses or social workers prepared by attending the three-day national “Family Donation Conversation” workshops, and the half-day NSW Simulation Program. The design is pre-post intervention to compare rates of family consent for organ donation six months before and under the intervention. Each ICU crosses from using the control to intervention condition after the site initiation visit. The primary endpoint is the consent rate for deceased organ donation calculated from 140 eligible next of kin families. Secondary endpoints are health professionals’ adherence rates to core elements of the intervention; identification of predictors of family donation decision; and the proportion of families who regret their final donation decision at 90 days.

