## Background

Organ and tissue transplantation is the definitive treatment for people with a wide range of end-stage organ failures. Escalating worldwide demand continues to drive efforts in many countries to increase the rate of deceased organ donation [1]. In Australia in 2011 the annual rate of deceased organ donation (15.1 donors per million population, dpmp) was below similar countries in the developed world such as the United Kingdom (UK) (17 dpmp), and international leaders such as the United States of America (USA, 25.9 dpmp), and Spain (35.9 dpmp) [2].

In New South Wales (NSW), Australia, consent for organ donation must be provided either from the patient while living or, when incapacitated, from the senior available next-of-kin (SaNOK): that is, a relative identified in line with an agreed family hierarchy [3]. In NSW the annual consent rate increased from 51% in 2011 [4] to 62% in 2013 [*unpublished 2014 NSW Organ and Tissue Donation Service (OTDS) data*], contributing to an annual national increase from 57% [5] to 61% [6] respectively. Other countries with similar health systems such as the UK, also reported a national consent rate of around 60% for 2013/14 [7]. Yet this consent rate is comparatively low in contrast to overwhelming positive public opinion in surveys of the UK and Australian populations with 90% and 69% respectively supporting donation and willing to become organ donors, describing predominantly altruistic beliefs on the topic [7–9]. Furthermore the consent rate decreased to 29% *[unpublished 2011 NSW OTDS data]* when families have been offered organ donation at the hospital and the patient had not previously registered their donation decision.

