### Design

This is a pre-post intervention design where rates of consent for organ donation for at least six months before implementation of the program in each ICU will be compared to the rates of consent for organ donation under the intervention.

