#### To address the primary endpoint

Consent rates provided by the next of kin for organ and tissue donation where the potential donor had not registered their decision will be calculated.

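### The 140 families and 80% power belong to a one-sample test against a fixed 29%, not to the pre-post comparison with usual practice that the design and hypothesis describe

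*Protocol article*

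**What the plan says.** **Comparative statements.** The Abstract states: "The design is pre-post intervention to compare rates of family consent for organ donation six months before and under the intervention". The Design section says that rates from at least six months before implementation in each ICU "will be compared to the rates of consent for organ donation under the intervention". Under Aims and hypothesis, the comparator is current usual practice.

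**Sample size.** The Statistical methods section names Simon's two-stage design and states that "140 eligible next of kin families are required to be approached to provide consent for organ donation". It continues: "This will yield 80% power with 95% confidence to exclude a consent rate of 29% in favour of a clinically worthwhile rate of 40" per cent for the intervention. The interim look is worded "in the first 46 eligible next of kin families who are approached, if less than 15 have consented to organ donation", in which case modification of the study will be considered. Background gives the source of the 29%: unpublished 2011 state data for the situation "when families have been offered organ donation at the hospital and the patient had not previously registered their donation decision".

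**Analysis.** Under the primary endpoint heading the only statement is: "Consent rates provided by the next of kin for organ and tissue donation where the potential donor had not registered their decision will be calculated". The comparison of the period before site initiation with the intervention period comes later, under Additional analysis: consent rates over time.

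**The concern.** A Simon design treats the null rate as a known constant. It needs no control families and allows nothing for sampling error in a control rate. A pre-post comparison estimates both rates, so its uncertainty is larger. The article's only sample size and only power therefore belong to a test that the design and hypothesis do not describe, and the comparison they do describe has neither.

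Two misreadings could follow. A pre-post result that is not significant could be taken as evidence of no effect from a study thought to have 80% power. A result above 29% could be taken as superiority to usual practice when it shows only superiority to a 2011 figure.

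**Working it through.** **1. Reproducing the article's figure**

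Inputs from Statistical methods: null rate 0.29, target rate 0.40, first stage 46 families (14 or fewer consents fails), total 140. The final cut-off is not stated; 50 or more consents is the value that reproduces the claim.

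P(success | p) = sum over x = 15 to 46 of P(X1 = x | 46, p) × P(X2 ≥ 50 − x | 94, p)

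- p = 0.29: 0.0416 (one-sided type I error)
- p = 0.40: 0.8002 (power)

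The stated 80% is reproduced as a one-sample test at one-sided 5%.

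**2. Effect of a non-binding first stage**

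The interim rule only prompts consideration of a change. If the study always continues to 140, the cut-off changes:

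| Cut-off | P(success) at 0.29 | P(success) at 0.40 |
|---|---|---|
| 50 or more of 140 | 0.0507 | 0.869 |
| 51 or more of 140 | 0.035 | 0.828 |

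Without a binding stop, 51 is the smallest cut-off that keeps one-sided 5%.

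**3. Power of the pre-post comparison**

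Inputs: 140 intervention families, 0.29 against 0.40 (both from the article), independent families. The control count m is **assumed** to be 30 to 140, because the article does not give it.

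- p̄ = (0.29m + 0.40 × 140)/(m + 140)
- s0 = √[p̄(1 − p̄)(1/m + 1/140)]
- s1 = √[0.29 × 0.71/m + 0.40 × 0.60/140]
- power = Φ[(0.11 − z·s0)/s1], with z = 1.960 (two-sided 5%) or 1.645 (one-sided 5%)

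For m = 140, p̄ = 0.345, s0 = 0.0568 and s1 = 0.0564. Two-sided power is Φ(−0.024) = 0.490 and one-sided power is Φ(0.293) = 0.615.

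For m = 30, p̄ = 0.381, s0 = 0.0977 and s1 = 0.0926. Two-sided power is Φ(−0.879) = 0.190 and one-sided power is Φ(−0.547) = 0.292.

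| Control families (assumed) | Two-sided 5% | One-sided 5% |
|---|---|---|
| 30 | 19% | 29% |
| 70 | 34% | 47% |
| 140 | 49% | 62% |
| 200 (sensitivity) | 56% | 68% |

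With equal groups, 80% power needs 292 families per period two-sided or 230 one-sided. With 140 intervention families, one-sided power reaches 80% at about 581 controls. Two-sided power only approaches 80% as the control count grows without limit.

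**4. Expected precision of the pre-post difference**

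Half-width of the 95% interval = 1.96 × s1.

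- m = 140: 1.96 × 0.0564 = 0.111, about 11 points
- m = 60: 1.96 × 0.0717 = 0.141, about 14 points

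**5. Sensitivity to the fixed benchmark**

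Background reports overall state consent of 51% in 2011 and 62% in 2013. The rate in the unregistered subgroup after 2011 is not given. As an illustration only, suppose it had drifted to 35% under usual practice. Then P(X ≥ 51 | 140, 0.35) = 0.39, so the one-sample rule would declare success about 39% of the time with no intervention effect.

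**The case against.** The strongest defence is that the sample size sentence is true as written. It names a one-sample method and claims only to exclude 29%. The Abstract describes the primary endpoint as a rate calculated from 140 families, the Endpoints section defines it as a rate, and the pre-post comparison is labelled additional. On that reading the primary analysis is single-arm against a benchmark, and the article never attaches 80% to the pre-post contrast.

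Much of this stands: there is no arithmetic error. But the single-arm reading leaves the stated hypothesis, against current usual practice, without a primary analysis. An unseen analysis plan could add detail, but it would not remove a conflict between sections of this article.

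Two stronger readings are tempting but not supported:

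- A reader might infer that the study has 19% to 49% power. That range is not in the article. It rests on an assumed 30 to 140 controls and a two-sided test, whereas the article's own figure reproduces one-sided. The control period is at least six months per site, so 140 is not an upper limit.
- A reader might infer that 95% confidence promises a two-sided interval and that the stated power therefore fails. Simon designs are conventionally one-sided, and the article promises no such interval.

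**Conclusion.** The concern holds as a mismatch between sample size, primary analysis and hypothesis. The 140 families and 80% power are correct for a one-sided 5% test against a fixed 29%, and for nothing else in the article. The comparison with the sites' own usual practice has no stated size or power and is not the primary analysis.

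For that comparison, power is about 19% to 49% two-sided or 29% to 62% one-sided, below 80% either way. This assumes 30 to 140 control families, true rates of 29% and 40%, and independent families. Clustering within the nine ICUs is left out because no intracluster correlation is given.

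Exceeding 29% would not establish superiority to current usual practice. The article's overall consent rates rose after 2011, and its Discussion accepts that national training may raise consent independently of the intervention. The documents do not show how far the rate in unregistered patients moved, so the size of that bias is unknown.

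**What to change.** 1. In Statistical methods, state that 140 families and 80% power apply only to the one-sided 5% one-sample test against 29%, and not to the pre-post comparison.
2. If a success cut-off is given, use 51 or more of 140 while the first-stage look is non-binding. A cut-off of 50 or more is valid only if the first-stage stop is made binding.
3. Under the primary endpoint heading, make the pre-post difference in consent rate among families of unregistered patients, with its 95% confidence interval, the primary analysis. The test against 29% can remain as a benchmark.
4. Report the expected half-width of that interval from the actual control count, which can be extracted from the retrospective data.

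The cost is rewording and a less favourable stated power. No extra patients are needed.

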## Methods/Design

### Aims and hypothesis

The aim of this study is to examine the process of organ donation decision-making, and to test whether changes in requesting practices change rates of family consent for organ donation and other family-based outcomes. A secondary aim is to examine whether changes in requesting practices result in increased satisfaction by families with their donation decision. The hypothesis for the trial component is that, compared to current usual practice, a ‘best practice’ family approach intervention will increase the family consent rate for deceased organ donation.

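### The only powered criterion tests against a fixed 2011 rate of 29%, while the hypothesis is superiority to current usual practice at the same sites, a comparison left as an unpowered additional analysis

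*Protocol article*

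**What the plan says.** **Sizing.** Protocol article, Statistical methods: "The sample size calculation was performed using the Simon’s two-stage design". The aim is to "exclude a consent rate of 29% in favour of a clinically worthwhile rate of 40% for the intervention", using 140 eligible families, and "This will yield 80% power with 95% confidence". If fewer than 15 of the first 46 families consent, modifying the study will be considered. Eligible families are those of patients who had not registered a decision.

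**Source of the 29%.** Background: "Furthermore the consent rate decreased to 29% *[unpublished 2011 NSW OTDS data]* when families have been offered organ donation at the hospital", for patients with no registered decision. The same paragraph says "In NSW the annual consent rate increased from 51% in 2011 [4] to 62% in 2013". That is the overall rate, not the rate in unregistered patients.

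**Hypothesis and design.** Aims and hypothesis: relative to current usual practice, the intervention "will increase the family consent rate for deceased organ donation". Design describes a pre-post comparison using at least six months before implementation in each ICU.

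**Analysis.** The paragraph on the primary endpoint says only that consent rates in the unregistered group will be calculated, and names no comparator. The before-and-after comparison stands under the additional analysis of consent rates over time. It has no power statement and no stated restriction to unregistered patients. Rates in non-participating NSW hospitals are to be presented over time.

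**Acknowledged threat.** The Discussion accepts that national conversation training may raise consent independently of the study, and that the effect of community education on registration cannot be gauged.

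**The concern.** The article powers one question and hypothesises another. The 29% is a 2011 figure, the trial was registered in July and August 2013, and the national training programme began in October 2011. The claimed 95% confidence protects against a false claim of superiority to usual practice only if usual practice among unregistered families at the nine sites is still 29%. If that rate has risen for any other reason, the rise counts towards meeting the criterion.

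The Discussion's reply to this threat is that consent should rise faster under intervention than under control. A test of one rate against a constant cannot show that. At stake is whether a positive result on the sole powered criterion could be read as evidence for the stated hypothesis.

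**Working it through.** **Inputs.** p0 = 29%, p1 = 40%, N = 140, first stage 46 with at least 15 consents, 80% power, 95% confidence (Statistical methods). I read the 140 as intervention-period families, because the 40% is the target under the intervention. Overall NSW rates of 51% (2011) and 62% (2013) come from Background. The final cut-off c and the sidedness of the test are not stated.

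**1. Reproduce the plan's figure.** With exact binomial probabilities,

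P(pass | p) = Σ over x = 15 to 46 of C(46, x) p^x (1 − p)^(46 − x) × P[Bin(94, p) ≥ c − x].

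The smallest c with one-sided error of at most 5% is 50: c = 49 gives 0.057 and c = 50 gives 0.042 at p = 0.29. At p = 0.40, c = 50 gives 0.800. The stated 80% power reproduces, so the arithmetic for N = 140 is sound as a one-sample design.

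**2. Candidate background rates in unregistered families.** The documents give no rate after 2011, so these are assumptions:
- No drift: 29%.
- A three-point drift: 32%.
- Overall rise applied as a ratio: 0.29 × 62/51 = 0.353.
- Overall rise applied as an odds ratio: (0.29/0.71) × (62/38)/(51/49) = 0.640, and 0.640/1.640 = 0.390.
- Overall rise applied as points: 0.29 + 0.11 = 0.40, which equals the whole target effect.

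**3. Probability of passing with no intervention effect.** The second column uses c = 52, the smallest count whose two-sided exact 95% interval excludes 29% (lower limit 28.5% for 51/140 and 29.1% for 52/140).

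| True background | c = 50 | c = 52 |
|---|---|---|
| 29% | 4.2% | 2.0% |
| 32% | 16.5% | 10.0% |
| 35.3% | about 42% | about 32% |
| 39.0% | 74% | 65% |
| 40% | 80% | 73% |

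The first-stage rule is only a prompt to consider changes. If the study always continues to 140, the c = 50 figures are higher: 5.1% at 29%, 19.6% at 32% and about 49% at 35.3%.

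**4. Power of the comparison that the hypothesis needs.** For 29% versus 40%, two-sided 5%, 80% power and equal periods, with pooled rate 0.345:

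n = [1.96 √(2 × 0.345 × 0.655) + 0.842 √(0.29 × 0.71 + 0.40 × 0.60)]² / 0.11² = (1.318 + 0.562)² / 0.0121 ≈ 292 per period.

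With 140 per period, the standard error is √(0.345 × 0.655 × 2/140) = 0.0568 under the null and √(0.4459/140) = 0.0564 under the alternative. Power is Φ[(0.11 − 1.96 × 0.0568)/0.0564] = Φ(−0.02) ≈ 49%. The baseline size is not given. With 140 in the intervention period, a baseline of 100 gives about 42%, 70 about 34% and 50 about 27%.

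**The case against.** The strongest reply has four parts.

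**The trend figures describe another population.** The rise from 51% to 62% covers all potential donors, while the primary endpoint covers unregistered patients. The overall rate can rise because more people register, and the Discussion mentions community education with that aim. A reader might infer that the protocol's own figures show the benchmark to be out of date, or that the trial would succeed on trend alone. The documents do not support that: no later rate for unregistered families is given, and with no drift the error rate is the planned 4.2%. This part stands.

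**The success rule is inferred.** No final cut-off is written, and the formal test may be in a document not shown. This limits the precision of the probabilities. It does not remove the risk, since the stricter cut-off shows the same pattern.

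**The comparison is already planned.** A reader might infer that the protocol ignores usual practice or trend. It does not. Pre-initiation data are extracted, a before-and-after comparison is listed, state-wide data are collected and the threats are discussed. But these analyses have no power statement. In addition, the planned contrast of trained with never-trained hospitals is limited to families approached before training was introduced, so it cannot control for trend during the intervention.

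**A plain pre-post test is also open to trend.** This is correct and shapes the fix. So is the related point that putting an estimated baseline into a one-sample test as if it were known would ignore its sampling error.

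The article also does not say that the 29% comes from all NSW hospitals rather than the nine sites. It says only that these are NSW service data.

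**Conclusion.** The concern holds as a mismatch between the powered criterion and the hypothesis. The sample size is correct for a one-sample test against 29%, but meeting that criterion would not establish superiority to current usual practice at the study sites. The chance that an ineffective intervention meets it is 2% to 4% if the 2011 rate still holds, 10% to 16.5% after a three-point drift, about 32% to 42% at 35.3%, and 65% to 74% at 39% (cut-offs of 52 and 50).

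These figures rest on the inferred cut-offs, on independent families, and on assumed background rates. The two highest rates assume that unregistered families shared the overall NSW rise, which the article neither states nor rules out. That the criterion cannot separate intervention from background does not depend on those assumptions.

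**What to change.** - Make the primary efficacy analysis the two-sample comparison, in unregistered families, of the intervention period with the nine sites' own pre-initiation period. Report the difference with a confidence interval that carries the sampling error of both periods.
- Use the data already collected from non-participating NSW hospitals, over the same calendar time and in unregistered patients, as a concurrent control for trend.
- Report the comparison with 29% as historical context that does not attribute effect. Do not substitute the estimated baseline for 29% as a known constant in a one-sample test.
- State that the 80% power applies only to the one-sample test against 29%. Give the power of the two-period comparison: about 49% with 140 families per period, and less if the six-month baseline is smaller.
- Align the sections on sample size, primary endpoint and consent rates over time with this.

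**Cost.** Mainly wording, since the site baseline and state-wide data are already being collected. The price is a less favourable stated power and a wider interval. At 40% with 140 families, the 95% half-width is 1.96 × √(0.24/140) = 8.1 points for the single rate. For the difference from a 29% baseline of equal size it is 1.96 × 0.0564 = 11.1 points, and adjustment for trend would probably widen it further.
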